**Infections**		
Aspergillosis, other invasive	CXR abnormality compatible with aspergillosis PLUS invasive mycelia consistent with Aspergillus on lung biopsy or positive culture of lung tissue or positive culture of sputum	CXR abnormality compatible with aspergillosis PLUS invasive mycelia consistent with Aspergillus on lung biopsy PLUS positive culture of lung tissue or positive culture of sputum
Bartonellosis	Clinical evidence of bacillary angiomatosis or bacillary peliosis PLUS positive silver stain for bacilli from skin lesion or affected organ	Clinical evidence of bacillary angiomatosis or bacillary peliosis PLUS positive culture or PCR for *Bartonella quintana* or *Bartonella henselae*
Candidiasis of bronchi, trachea or lungs	None	Macroscopic appearance at bronchoscopy or histology or cytology (not culture)
Candidiasis, oesophageal	Recent onset retrosternal pain on swallowing PLUS clinical diagnosis or oral candidiasis by cytology (not culture) PLUS clinical response to treatment	Macroscopic appearance at endoscopy or histology or cytology (not culture)
Coccidiodomycosis, disseminated or extrapulmonary	None	Histology or cytology, culture or antigen detection from affected tissue
Cryptococcosis, meningitis or pulmonary	None	Histology or cytology/microscopy, culture or antigen detection from affected tissue
Cryptosporidiosis	None	Persistent diarrhoea >1 month, histology or microscopy
CMV retinitis	Typical appearance on fundoscopy of discrete patches of retinal whitening, associated with vasculitis, haemorrhage, and necrosis, confirmed by ophthalmologist	None
CMV end-organ disease	None	Compatible symptoms plus histology or detection of antigen from affected tissue
**Infections**	**Presumptive criteria**	**Definitive criteria**
CMV radiculomyelitis	Leg weakness and decreased reflexes or syndrome consistent with cord lesion presenting subacutely over days to weeks. CT/MRI shows no mass lesion. CSF shows >5 WBC with >50% polymorphs and positive CMV PCR, antigen or culture	None
CMV meningoencephalitis	Rapid (days to <4 weeks) syndrome with progressive delirium, cognitive impairment, ± seizures and fever (often with CMV disease elsewhere) CT/MRI may show periventricular abnormalities.	Rapid (days to <4 weeks) syndrome with progressive delirium, cognitive impairment, ± seizures and fever (often with CMV disease elsewhere) CT/MRI may show periventricular abnormalities and CSF PCR positive for CMV
HSV mucocutaneous ulceration	None	Persistent ulceration for >1 month, plus histology or culture or detection of antigen or HSV PCR positive from affected tissue
HSV visceral disease (for example, oesophagitis, pneumonitis	None	Symptoms, plus histology or culture or detection of antigen or HSV PCR positive from affected tissue
VZV multidermatomal	≥10 typical ulcerated lesions affecting at least two noncontiguous dermatomes plus response to an antiviral active against VZV unless resistance is demonstrated	≥10 typical ulcerated lesions affecting at least two noncontiguous dermatomes plus culture or detection of antigen or VZV PCR-positive from affected tissue
Histoplasmosis, disseminated or extrapulmonary	None	Symptoms plus histology or culture or detection of antigen from affected tissues
Isosporiasis	None	Persistent diarrhoea for >1 month, histology or microscopy
Leishmaniasis, visceral	None	Symptoms plus histology
Microsporidiosis	None	Persistent diarrhoea for >1 month, histology or microscopy
MAC, and other atypical mycobacteriosis	Symptoms of fever, fatigue, anaemia or diarrhoea plus acid-fast bacilli seen in stool, blood, body fluid, or tissue but not grown on culture and no concurrent diagnosis of TB except pulmonary	Symptoms of fever, fatigue, anaemia or diarrhoea plus culture from stool, blood, body fluid, or tissue
Tuberculosis, pulmonary	Symptoms of fever, dyspnoea, cough, weight loss, fatigue plus acid-fast bacilli seen in sputum, lavage, or lung tissue, not grown in culture, plus responds to standard TB treatment	Symptoms of fever, dyspnoea, cough, weight loss, fatigue plus positive TB culture or PCR from sputum, bronchial lavage, or lung tissue
Tuberculosis, extrapulmonary	Symptoms, plus acid-fast bacilli seen from affected tissue or blood but not grown in culture, concurrent diagnosis of pulmonary TB or responds to standard TB treatment	Symptoms, plus positive TB culture or PCR from affected tissue
Nocardiosis	Clinical evidence of invasive infection plus microscopic evidence of branching, Gram-positive, weakly acid-fast bacilli from affected tissue	Clinical evidence of invasive infection plus positive culture from blood or affected tissue
*Penicillium marneffei* disseminated	Characteristic skin lesions plus response to antifungal therapy for penicilliosis (in an endemic area)	Culture from a nonpulmonary site
*Pneumocystis* pneumonia (PCP)	Symptoms, any CXR appearance and CD4 count <200, negative bronchoscopy if treated for PCP for >7 days, no bacterial pathogens in sputum, and responds to PCP treatment	Microscopy or histology
Extrapulmonary pneumocystis	None	Symptoms plus microscopy or histology
Recurrent bacterial pneumonia	Second pneumonic episode within 1 year, new CXR appearance, symptoms and signs, diagnosed by a doctor	Second pneumonic episode within 1 year, new CXR appearance, detection of a pathogen
Progressive multifocal leukoencephalopathy (PML)	Symptoms and brain scan consistent with PML and no response to treatment for toxoplasmosis	Symptoms and brain scan consistent with PML and positive JC virus PCR in CSF or histology
*Rhodococcus equi* disease	None	Clinical evidence of invasive infection plus culture of organism from blood or affected tissue
Recurrent *Salmonella* septicaemia	None	Second distinct episode, culture confirmed
Cerebral toxoplasmosis	Symptoms of focal intracranial abnormality or decreased consciousness, and brain scan consistent with lesion(s) having mass effect or enhancing with contrast, and either positive toxoplasma serology or response to treatment clinically and by scan	Histology or microscopy
Extra-cerebral toxoplasmosis	None	Symptoms plus histology or microscopy

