#### Immunosuppression

Corticosteroids are immunosuppressive. It is possible that they may slow yeast clearance from CSF, and increase the risk of other infections. However, animal studies suggest that dexamethasone improves yeast clearance from CSF [14]. Even if the rate of yeast clearance is reduced, this may not be detrimental. In this study, we will measure the rate of clearance of yeast from CSF (see Appendix 1). Patients with CM are profoundly immunosuppressed: the median CD4 count in Vietnamese patients is 16 cells/μl (which compares with a median CD4 count of 42 in Vietnamese HIV patients with tuberculous meningitis) [38]. Given this, whether dexamethasone will significantly increase the risk of other opportunistic infections (OIs) is not clear. The incidence of other OIs is a secondary end point of the study. Patients in the study will receive chemoprophylaxis against *Pneumocystis jirovecii* and other opportunistic infections, in line with national guidelines. Patients will be screened for TB at study entry as part of normal care.

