### Randomisation

Randomisation will be 1:1 to either dexamethasone or identical placebo. Patients will be stratified by hospital of enrolment. Enrolment logs specific to each site will be used to assign patients to the next available sequential number. The assigned number will correspond to a blinded, sealed, treatment pack containing dexamethasone for injection and dexamethasone tablets, or visually identical placebos. Treatment packs will be prepared centrally by an unblinded study pharmacist and distributed to the sites in batches, as required. Only central study pharmacists who hold the master randomisation list will know the contents of each pack. This list will be accessed only in the case of emergency unblinding, authorised by an investigator or designee, as per standard operating procedures. At each site we will use block randomisation with variable block lengths of size 4 (with probability 0.75) or 6 (with probability 0.25), respectively. Stratification by site will minimise the effect of any differences in patient or health care characteristics by ensuring that nearly equal numbers of patients receive either of the two treatment arms at each site. Drug appearance and administration schedules will be identical to maintain blinding amongst the attending physicians and nurses.

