## Statistics

### Sample size and power considerations

The trial is powered for the primary end point (that is, overall survival during the 10-week follow-up period).

Few data exist on which to estimate the potential effect size of dexamethasone on mortality from CM. We have based our estimate of the effect size on data from tuberculous meningitis, which shares clinicopathologic features with CM. In a large RCT of dexamethasone to treat tuberculous meningitis in Vietnam, the hazard ratio (HR) for death was 0.69 at 9 months in favour of dexamethasone [25]. Most of this effect occurred during the first 3 months of treatment. The dose of dexamethasone we will test is the same as that used in that trial. Additionally, in a study of dexamethasone in bacterial meningitis in Vietnam, the HR was 0.43 in patients with microbiologically confirmed disease, and 0.59 in a study based in Europe, again in favour of dexamethasone [34, 35]. These analyses were all based on the intention-to-treat principle (including noncompliant patients), and it seems sensible to expect a similar rate of noncompliance in our study. Therefore, we believe a target hazard ratio of 0.7 in favour of dexamethasone to be reasonable for our trial.

To detect such a risk reduction of 30% with 80% power at the two-sided 5% significance level, a total of at least 247 deaths must be observed. Based on historical data and consultation with principal investigators from all study sites, the 10-week mortality risk in the control group is expected to be between 30% and 50% [38], and the target hazard ratio of 0.7 corresponds to absolute risk reductions in mortality from 30% to 22%, or from 50% to 38%. Assuming an overall 10-week mortality of at least 30% in our study population, recruitment of 824 patients is sufficient to observe the target number of deaths. Allowing for some loss to follow-up, the total sample size for this study is 880 patients.

A major aim of this trial is to generate robust evidence across both continents. To achieve this goal, we aim to recruit roughly similar numbers of patients from each continent.

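### Table 5's presumptive CMV meningoencephalitis criterion needs no CMV evidence and excludes no other cause, so worsening of the index cryptococcal meningitis can count as a new AIDS-defining illness

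*Protocol article*

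**What the plan says.** All participants have cryptococcal meningitis at entry, shown by CSF India ink, culture from CSF or blood, or CSF antigen (Inclusion criteria). Because steroids are immunosuppressive, the section on Immunosuppression states: "The incidence of other OIs is a secondary end point of the study". Secondary aims repeats the incidence of other opportunistic infections as an aim.

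Clinical monitoring has sites watch for new or recurrent AIDS-defining illnesses by Table 5, and Assessment of adverse events also defines new AIDS-defining events by Table 5. The end-point section (Time to new AIDS-defining illnesses or death until 10 weeks) instead points to the WHO list in Table 2, whose note accepts presumptive diagnoses. The planned analysis is a Cox model for new AIDS-defining illness or death (Analysis of secondary end points).

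The relevant rows of Table 5 are:

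- **CMV meningoencephalitis, presumptive:** "Rapid (days to <4 weeks) syndrome with progressive delirium, cognitive impairment, ± seizures and fever (often with CMV disease elsewhere"), with optional imaging findings. The definitive column has the same text plus a positive CSF PCR.
- **Cryptococcosis, meningitis or pulmonary:** no presumptive criterion; the definitive one is "Histology or cytology/microscopy, culture or antigen detection from affected tissue".
- **Cerebral toxoplasmosis, presumptive:** symptoms, a lesion on brain scan, "and either positive toxoplasma serology or response to treatment clinically and by scan".

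**The concern.** The end point is meant to show whether dexamethasone brings more infections. The CMV meningoencephalitis row describes signs that worsening cryptococcal meningitis also produces, such as delirium, cognitive decline, seizures and fever. The rationale expects dexamethasone to reduce cerebral oedema and intracranial pressure, so it may change how often those signs appear. If they are filed as infections, a safety measure becomes partly an efficacy measure. Benefit on neurological worsening would pull the infection comparison down, and harm would push it up.

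The cryptococcosis row adds an ambiguity. Patients satisfy it on the day they enter, and repeated CSF cultures in the first two weeks are part of the trial at selected sites. Positive post-baseline samples are therefore expected, and the word recurrent in Clinical monitoring is left undefined for this row.

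**Working it through.** **1. The rows side by side.**

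| Table 5 row (presumptive unless stated) | CMV or other specific evidence needed? | Other causes excluded? | Can signs of the index disease alone meet it? |
|---|---|---|---|
| CMV meningoencephalitis | No | No | Yes |
| CMV radiculomyelitis | Yes, positive CMV PCR, antigen or culture | No | No |
| HIV encephalopathy | No | Yes, absence of another condition | No |
| HIV wasting | No | Yes | No |
| Cerebral toxoplasmosis | Scan lesion plus serology or treatment response | No | No, needs a scan and a further finding |
| Primary cerebral lymphoma | Mass lesion on scan and no response to toxoplasma treatment | No | No, needs a scan and a treatment course |
| Cryptococcosis (definitive only) | Microscopy, culture or antigen | No | Already met at entry |

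The CMV meningoencephalitis row is the exception. Neighbouring rows require specific evidence or an exclusion; this one requires neither. Brain imaging is not mandated (Imaging), which further limits the scan-based rows.

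**2. The protocol's own figures.** It gives no event rate or power for AIDS-defining illness. Its primary-end-point figures reproduce: 4 × (1.960 + 0.842)² / (ln 0.7)² = 246.8, so 247 deaths; 247 / 0.30 = 823.3, so 824 patients. They do not bear on this point beyond supplying the mortality (30%) and hazard ratio (0.7) used in step 5.

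**3. Illness-only dilution.** Let s be the share of control-arm recorded illnesses that are really index-disease worsening. With proportional hazards for each part,

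observed HR = (1 − s) × HR(infection) + s × HR(worsening).

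Assume HR(infection) = 1.5 and HR(worsening) = 0.7:

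- s = 10%: 0.90 × 1.5 + 0.10 × 0.7 = 1.42
- s = 25%: 0.75 × 1.5 + 0.25 × 0.7 = 1.30
- s = 50%: 0.50 × 1.5 + 0.50 × 0.7 = 1.10

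The share that brings the observed ratio to 1 is (1.5 − 1) / (1.5 − 0.7) = 62%. With an infection HR of 1.3 it is (1.3 − 1) / (1.3 − 0.7) = 50%. Over infection HRs of 1.2 to 1.5 and worsening HRs of 0.5 to 0.7 it ranges from 29% to 62%.

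The reverse case: no infection effect (HR 1.0), worsening HR 1/0.7 = 1.43 and s = 25% give 0.75 × 1.0 + 0.25 × 1.43 = 1.11, an apparent excess where none exists.

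**4. Power to see the excess, illness only.** Assume 440 per arm, HR(infection) 1.5, HR(worsening) 0.7, death ignored, and power = Φ(√(events/4) × ln HR − 1.96).

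| Assumed control infection risk | s = 0 | s = 10% | s = 25% | s = 50% |
|---|---|---|---|---|
| 10% | 56% | 47% | 32% | 9% |
| 20% | 84% | 75% | 55% | 14% |

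**5. The planned composite with death.** The cumulative hazards in control are 0.357 for death (−ln 0.70) and 0.105 for infection (−ln 0.90, assumed risk 10%).

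- No misclassification: (0.357 × 0.7 + 0.105 × 1.5) / (0.357 + 0.105) = 0.88.
- Misclassified worsening in 5%, 10% or 20% of control patients (hazards 0.051, 0.105, 0.223; HR 0.7): 0.86, 0.85, 0.82. These correspond to s of about 33%, 50% and 68%.
- At s = 10% and 25% (worsening hazards 0.012 and 0.035) the composite is 0.88 and 0.87.

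With an assumed infection risk of 20% (hazard 0.223), the composite is (0.250 + 0.335) / (0.357 + 0.223) = 1.01 without misclassification and 0.97 at s = 25%.

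**The case against.** The strongest objection is that the planned analysis is illness or death. There, step 5 shows that an infection HR of 1.5 already appears as about 0.88 with perfect classification (1.01 at the higher infection risk). Mortality does most of the masking, and repairing Table 5 would not restore the signal. This stands. It confines the harm mainly to the incidence of opportunistic infections, which Immunosuppression and Secondary aims name in their own right.

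A reader might also infer that Table 5's presumptive criteria in general absorb the index disease, or that the flaw is bound to hide an infection excess. The document supports neither reading. Only one presumptive row can be met by clinical signs alone; toxoplasmosis and lymphoma need a scan and a further finding, and cryptococcosis has no presumptive criterion. The bias runs in either direction, and complete masking needs a large misclassified share.

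It is also fair to say that a clinician, blinded to allocation, has to make the diagnosis; that the word new should exclude persisting CSF positivity on a sensible reading; and that specific adverse events are summarised by arm, so an excess of tuberculosis or pneumocystis pneumonia could still be seen. These points lower the likely misclassified share. They do not alter the written criterion, and recurrent remains undefined for cryptococcosis.

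Finally, the end-point section cites Table 2, so Table 5 may not govern. But Table 2 supplies no diagnostic criteria for CMV disease of the brain, so Table 5 is the only working definition on the page. A separate analysis plan might restrict the event derivation; the criterion as stated here would still be wrong for recording.

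**Conclusion.** The point holds for the presumptive CMV meningoencephalitis row and, as an ambiguity, for the cryptococcosis row. As written, deterioration of the disease that every participant has can be counted as a new AIDS-defining illness, and a treatment effect on that deterioration can enter the opportunistic-infection comparison in either direction.

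The size cannot be derived from the protocol. On the assumed hazard ratios, an illness-only ratio of 1.5 is diluted to between 1.42 and 1.30 at misclassified shares of 10% to 25%; it is not removed. The composite with death moves little: from 0.88 to no lower than 0.82 even with misclassified worsening in 20% of control patients, at an assumed infection risk of 10%. The primary end point is untouched. This is a worthwhile correction to a safety-relevant secondary end point, not a threat to the trial's main conclusion.

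**What to change.** 1. In the presumptive CMV meningoencephalitis row of Table 5, require CMV evidence, or state that the syndrome is not explained by cryptococcal disease (meningitis, raised intracranial pressure, relapse or IRIS).
2. State that persisting cryptococcal positivity from the index episode is neither a new nor a recurrent AIDS-defining illness. Deterioration from the index disease goes to the neurologic-event or relapse end point where it meets those definitions.
3. Reconcile the end-point section, which cites Table 2, with Clinical monitoring and Assessment of adverse events, which cite Table 5, and say which governs the analysis.
4. Leave the toxoplasmosis row as it is. Making it depend on treatment response would tie ascertainment to survival and oedema, both of which dexamethasone may change, and so could make it differ by arm.

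The cost is an edit to Table 5 and its cross-references. It concerns event classification only: no added test and no change to patient care. The downside is that a few true CMV cases without CMV testing may go uncounted. If the CMV-evidence option is chosen, ascertainment will also depend on which sites can test; the exclusion wording avoids that.

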**Neoplasms**		
Kaposi sarcoma (KS)	Typical appearance without resolution. Diagnosis should be made by an experienced HIV clinician	Histology
Cervical carcinoma, invasive	None	Histology
Lymphoma, primary cerebral	Symptoms consistent with lymphoma, at least one lesion with mass effect on brain scan, no response to toxoplasma treatment clinically and by scan	Histology
Lymphoma, non-Hodgkin B cell	None	Histology
lymphoma, Hodgkin	None	Histology
**Neurologic**		
HIV encephalopathy	Cognitive or motor function interfering with usual activity, progressive over weeks or months in the absence of another condition to explain the findings. Should have a brain scan ± CSF examination to exclude other causes.	None
**Other**		
Indeterminate cerebral lesion (s)	Neurologic illness, with evidence for an intracerebral lesion by brain scan, where the differential diagnosis is either cerebral toxoplasmosis. PML, cerebral lymphoma, or HIV encephalopathy	

Based on 1993 Revised CDC classification system (MMWR 1992; 41(RR-17): 1-19) and modified for this trial.

Visual deficit (at week 10)IRISIncreased intracranial pressure (clinical or measured)

Uniform management of patients and recording of data will be ensured by the local study staff, who will do clinical assessments daily while admitted and at follow-up visits.

Disability and mortality at 6 months and evidence of morbidity (including IRIS) since last seen (week 10) will be collected with either a structured telephone interview or an outpatient visit. Outpatient visits may occur in the patient’s home when the patient cannot come to the hospital.

### Laboratory monitoring

Inpatient laboratory monitoring will be as shown in the study schedule (section Treatment of CM).

Other investigations may be performed as clinically indicated. Data for the following will be recorded when performed for routine clinical care:

CSF, if neurologic deterioration (Gram stain and routine culture, ZN stain and mycobacterial culture, India ink stain, and fungal quantitative culture)Sputum, if symptomatic (routine culture, ZN stain)Urine culture, if urinary symptoms (urine culture)Stool examination, if prolonged diarrhoea (microscopy, culture, and parasites)Blood cultures, if persistent feverLymph node aspiration (routine and mycobacterial cultures)Blood glucose will be measured when CSF is examined or if hyperglycaemia is suspected

A window period of ±2 days outside of the scheduled laboratory tests will apply to all tests that are not baseline inclusion/exclusion criteria.

### Imaging

A chest radiograph must be performed on study entry if it has not been done at the time of diagnosis. The result will be recorded in the CRF. Brain imaging is not mandated by the study. The decision to perform brain imaging will be according to local practice. Results of brain imaging, when available, will be recorded.

### Management of adverse events

Possible side effects of dexamethsone were described earlier.

Given the experience from tuberculous meningitis, gastrointestinal haemorrhage is extremely unlikely (it occurred more frequently in placebo recipients than in patients receiving dexamethasone in the large randomised controlled trial from Vietnam). Gastrointestinal haemorrhage will be treated as per local practices, with cardiovascular support and proton pump inhibitors or H_2_ antagonists. Hyperglycaemia will be managed with insulin.

### Stopping study drug and unblinding rules

The purpose of the randomised, double-blind design of the trial is to protect the results from the potential influence of study staff or patient bias about which treatment is the most effective.

Occasionally it can be necessary to STOP the study intervention (placebo or dexamethasone) or to UNBLIND the patient’s treatment allocation.

*Note:*

*STOPPING* study drug does not necessitate *UNBLINDING* the treatment allocation. *UNBLINDING* treatment is not necessarily an indication to *STOP* treatment.STOPPING or UNBLINDING a patient’s treatment does not mean that they have withdrawn from the study. Patients continue in the study and follow the protocol schedule for visits and investigations until its conclusion at 6 months of follow-up.

